## 7.2 Consent

The Principal Investigator (PI) will retain overall responsibility for the informed consent of participants at site and will ensure that any person delegated responsibility to participate in the informed consent process is duly authorised, trained and competent to participate according to the ethically approved protocol, principles of Good Clinical Practice (GCP) and Declaration of Helsinki.

Informed consent will be obtained prior to the participant undergoing procedures that are specifically for the purposes of the trial and are outside standard routine care. The participant will remain free to withdraw at any time from the trial without giving reasons and without prejudicing his/her further treatment. Where a participant is required to re-consent or new information is required to be provided to a participant it will be the responsibility of the PI to ensure this is done in a timely manner.

The PI takes responsibility for ensuring that all vulnerable subjects are protected and participate voluntarily in an environment free from coercion or undue influence.

Consent will be received by the PI or co-investigator and will be obtained during the Screening Visit. Adequate explanation of the aims, methods, objectives and potential hazards of the study will be

provided to potential participants. A participant information sheet will be provided and adequate time allowed for questions and to consider the study, as well as to consider options for treatment outside the study, before agreeing to participate. Each participant will sign a consent form, a copy will put in the medical notes, one copy filed in the study centre file and the participant will be provided with a copy. If they decline to take a copy this will be documented in their medical notes.

### **7.3 The randomisation scheme**

After written informed consent has been received and eligibility established, subjects will be randomised 1:1 into the maraviroc and non-maraviroc groups (Groups A and B respectively) at the baseline visit (day 1). In addition, there will be stratification according to (1) current exposure or past history of  $\geq 6$  months exposure to protease inhibitor (PI)-containing antiretroviral therapy versus no current exposure and less than 6 months past exposure to PI-containing therapy and (2) BMI  $\geq 25$  versus  $< 25$  and (3) current exposure to a lipid-lowering agent and (4) being diabetic type 1 or 2 vs non-diabetic.

The rationale for this stratification is to attempt to reduce the potential for imbalance in factors considered a priori to be prognostic of ELF. Elevated BMI may be associated with faster progression of hepatic fibrosis in NAFLD patients. In addition, exposure to PI-containing therapy has in some studies been associated with accelerated fibrosis progression [1]. In other studies, lipid-lower therapies may reduce fibrosis progression [22]. Finally, diabetes mellitus has been identified as one of the strongest predictors of fibrosis progression in NAFLD patients [2].

The web-based Sealed Envelope™ system will be used to allocate individuals randomly to the maraviroc or non-maraviroc groups. The statistician will provide the randomisation list. The HEPMARc Randomisation Guide should be followed by the study team.

#### **7.3.1 Method of implementing the allocation sequence**

Sealed Envelope™ web based randomisation system will be used. Investigators randomise patients by completing an on-screen form with patient details, stratification factors, inclusion and exclusion criteria. Investigators are immediately shown the treatment allocation. Trial managers have real-time access to recruitment statistics and are notified by email of every new randomisation. The randomisation application conforms to the requirements of FDA 21 CFR part 11, Electronic Records; Electronic Signatures and ICH GCP.

No-one can delete records from the randomisation database, so that all randomisations have to be accounted for. Audit log files detailing all activity on the randomisation system are available to the trial manager.

### **7.4 Blinding**

Blinding will not be used. The rationale for this is:

- (1) This is a pilot study. However, if results do indicate a possible benefit of maraviroc in NAFLD, they may be used to inform the design of a larger, blinded placebo-controlled randomised controlled trial.
- (2) It is not considered likely that individuals in the maraviroc versus non-maraviroc group will differentially change their behaviour with respect to risk of fibrosis progression (eg dietary modifications, increase in exercise, reduction in alcohol consumption or other factor) and therefore the use of placebo is not considered essential for this pilot study.

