## 3 OBJECTIVES AND OUTCOME MEASURES/ENDPOINTS

### 3.1 Primary objectives

The primary objective will be to assess the feasibility and acceptability of the addition of maraviroc to OBT, versus maintenance of OBT alone, in the treatment of NALFD in people living with HIV. This will be assessed with respect to the following:

- a) Acceptability of recruitment into the study to eligible individuals
- b) Monthly participant recruitment rate
- c) Participant retention rate
- d) Completeness of the data set
- e) Proportion of individuals reporting adverse events
- f) Self-reported adherence to the study drug

The specific time points with respect to the above are provided in the 'primary measures' section below. The finding of confirmed feasibility and acceptability of the treatment approach of addition of maraviroc to effective cART in this population will support the establishment of larger, double-blind, placebo-controlled RCT to assess the efficacy of this intervention definitively.

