#### **Secondary endpoints:**

- a) Mean change in the ELF score by 48 and 96 weeks comparing the maraviroc and non-maraviroc groups.
- b) Mean change in Fibroscan stiffness by 48 and 96 weeks comparing the maraviroc and non-maraviroc groups

- c) Mean change in the Fibroscan Controlled Attenuation Parameter (CAP) score by 48 and 96 weeks comparing the maraviroc and non-maraviroc groups
- d) Change in the % with a CT liver:spleen attenuation ratio  $<1.0$  by 96 weeks comparing the maraviroc and non-maraviroc groups
- e) Mean change in blood-derived biochemistry by 48 and 96 weeks comparing the maraviroc and non-maraviroc groups: fasting HDL:chol ratio, LDL, HDL, TG, glucose, plus Hb1AC and ALT
- f) Mean change in clinical signs of the metabolic syndrome comparing the maraviroc and non-maraviroc groups by 48 and 96 weeks: BMI, waist circumference and weight
- g) Mean change in HIV parameters comparing the maraviroc and non-maraviroc groups: CD4 cell count and % with undetectable HIV VL.
- h) Differences in the quality of life of participants in the maraviroc and non-maraviroc groups by 48 and 96 weeks as assessed by responses to the chronic liver disease questionnaire for NAFLD (CLDQ:NAFLD), and the SF-36 and WPAI:SHP questionnaires.

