## 7.6 Trial assessments

Please see Table 1 for details of the timeline for trial visits and which procedures and assessments will be performed at each visit.

The following are recorded at the baseline visit and then every 24 weeks until the final visit at 96 weeks (i.e. day 1, week 24, week 48, week 72 and week 96):

- history and if necessary symptom-directed examination
- adherence to maraviroc as assessed by (i) self reported adherence through completion of a diary card and (ii) pill counting by pharmacy/research team member.
- weight and BMI
- waist circumference
- liver function, renal function, phosphate, CK, glucose (fasted at baseline, weeks 48 and 96), and lipid profile (fasted at baseline, weeks 48 and 96)(blood draw)
- FBC (blood draw)
- HIV viral load (blood draw)
- Urine dipstick macroanalysis and, for WOCBP, pregnancy testing

The following are recorded at the baseline visit and then every 48 weeks until the final visit at 96 weeks (i.e. day 1, week 48 and week 96):

- CD4/CD8 cell count and % (blood draw)
- HbA1c (blood draw)
- ELF score (blood draw)
- CLDQ:NAFLD questionnaire
- SF-36 questionnaire
- WPAI-SHP questionnaire
- Dietary and exercise history

The following is recorded at screen, week 48 and week 96:

- Fibroscan. For screening, the Fibroscan may be performed up to 42 days prior to baseline. For the week 48 and 96 visits this may be performed within 7 days of the study visit.

The following **optional investigation** will be performed at the baseline visit and at the 96 week visit:

- CT liver : spleen attenuation ratio. This may be performed within 7 days of the study visit with preference for the 7 days prior to baseline.

An additional week 4 safety visit will be required for those individuals in the maraviroc group, with the following procedures being performed:

- assessment of any drug toxicity through targeted history and, if required, examination
- liver function, renal function, CK, phosphate, glucose, full blood count (blood draw)
- HIV viral load (blood draw)

The following will be performed at screening only (if no hepatic imaging or liver biopsy result is available in the preceding 24 weeks):

- USS liver

The following will be performed at baseline only (if not available in the preceding 24 weeks):

- CCR5 tropism (blood draw)

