### 7.8 Storage and analysis of samples

Blood samples will be collected from patients at each study visit.

Routine biochemistry, haematology and virology testing will be performed through routine laboratory procedures. Samples will be delivered immediately within the internal courier system from the clinic room to the laboratory.

The following blood volumes will be required:

5mL gold top (SST) for LFTs, U+Es, lipids, phosphate, CK, and thyroid function

4mL EDTA for HbA1c

4mL EDTA for full blood count

5mL gold top (SST) for ferritin, copper, caeruloplasmin, alpha-1 antitrypsin, coeliac serology, and liver autoantibodies

2mL grey top (oxalate/fluoride) for glucose

2mL blue top (trisodium citrate) for INR

4mL EDTA for CD4/CD8 cell counts

5mL gold top (SST) for anti-HIV antibody/antigen, anti-HCV antibody, HCV antigen and HBsAg

8mL EDTA for HCV RNA

8mL EDTA for HIV RNA

8mL EDTA for HIV tropism

5mL gold top (SST) for ELF score (assays for TIMP-1, PIINP, HA) [*research bloods*]

For the ELF score, samples will be frozen at -80C and stored at site, as described in the Laboratory Manual, and at the end of the study, batched and couriered on dry ice to the Centre for Hepatology, University College London, and assayed for the three components noted above.

Blood for the tropism assay will be couriered from the pathology service to the relevant laboratory according to routine procedures.

Total maximum volume of blood for each visit is as below:

Screen 47mL, baseline 24mL, week 4 19mL, week 24 19mL, week 48 32mL, week 72 19mL, week 96 32mL, ETV 28mL

Total maximum volume of blood in the study will be: 192mL

No blood samples will be stored after they have been tested for the designated test, except for the viral serology and viral PCR blood samples; surplus samples from these specimens are, as a routine, stored on site for 2 years as part of clinical care for the purpose of retrospective viral testing, should this be required for the patient's subsequent care (eg HIV resistance testing).

Blood tubes for ELF score will be provided by the sponsor.

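### Section 7.4 rules out all blinding for reasons that do not concern outcome measurement, so follow-up Fibroscan and CT have no masked assessment

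*Protocol*

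**What the plan says.** Section 7.4 opens with "Blinding will not be used" and gives two reasons. The first is pilot status: "This is a pilot study. However, if results do indicate a possible benefit of maraviroc in NAFLD, they may be used to inform the design". The design meant there is that of a bigger trial with blinding and a placebo. The second is that the arms are not expected to change diet, exercise or alcohol intake differently, "therefore the use of placebo is not considered essential for this pilot study".

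Section 7.3.1 adds that "Investigators are immediately shown the treatment allocation". The secondary endpoints in section 3.3 include "Mean change in Fibroscan stiffness by 48 and 96 weeks comparing the maraviroc and non-maraviroc groups", the matching CAP comparison at both times, and the percentage with a CT liver:spleen ratio below 1.0 by week 96. Section 7.6 places the first Fibroscan at screening. On the later scans it says "For the week 48 and 96 visits this may be performed within 7 days of the study visit". The CT is optional, at baseline and week 96. Under section 7.8 the ELF samples are frozen and, "at the end of the study, batched and couriered on dry ice", sent to an outside laboratory for assay.

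**The concern.** An open-label trial can still have masked outcome assessment, because the two decisions are separate. Section 7.4 argues only about the first (whether a placebo is needed) but words its conclusion so that it also settles the second. No masked Fibroscan operator or CT reader is provided for here or anywhere else in the protocol. This is not a detail that a statistical analysis plan would supply: masking is a matter of trial conduct, and section 7.4 decides it in the negative.

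What is at stake is the between-arm comparison of stiffness, CAP and the CT ratio. Section 4 gives the trial's aim as feasibility and potential efficacy. Section 7.4 says a possible benefit may inform a larger trial. Section 13.10 says a beneficial effect may inform guidelines, and that a marked improvement in a participant's fibrosis markers is likely to strengthen the case for continuing the drug. The readings therefore carry consequences even though they are not primary outcomes.

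**Working it through.** The protocol gives no figure from which a bias could be calculated, so the check sets the sections side by side.

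**1. Do the stated reasons cover outcome measurement?** Pilot status affects how much is invested in blinding but says nothing about who reads a scan. Unchanged participant behaviour removes one route to bias, that of participants acting on knowledge of their arm. It leaves open the other route, that of assessors acting on it.

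**2. Can the arm be known at measurement?**
- Section 7.3.1: investigators see the allocation at randomisation.
- Sections 7.6 and 8.11: maraviroc pills are counted at study visits by a pharmacist or a research team member. The week 48 and 96 Fibroscans fall within 7 days of such visits.
- No section says who performs Fibroscan or reads the CT, and none keeps those people apart from staff who know the arm.
- Section 11.2: data are entered by study number, which keeps patient identity from the data management team. It does not mask an operator or reader.

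**3. Would a shift cancel?** Let b be the average shift in follow-up readings in the maraviroc arm and c that in the other arm. The first Fibroscan precedes randomisation, so knowledge of the arm cannot affect it. Then:

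- observed mean change, maraviroc arm = true change + b
- observed mean change, other arm = true change + c
- bias in the between-arm difference = b − c

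If an operator shifts both arms alike, b = c and nothing remains. If knowledge of the arm makes b differ from c, the whole of b − c enters the estimate. It does not shrink as the sample grows, and the confidence interval does not reflect it.

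**4. CT.** The baseline scan may fall within 7 days of the baseline visit, preferably before it, so it will often but not always precede allocation. The week 96 scan always follows it. The outcome is cut at 1.0. If k of m readings in one arm cross that cut, the arm's percentage moves by 100 × k/m points. Because the scan is optional, m is not known in advance. The 20 per group in section 10.1 is the number for the ELF analysis and cannot stand in for it.

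**5. ELF.** Section 7.8 has samples stored frozen, then batched and assayed at an outside laboratory after the study. No route by which that laboratory would learn the arm is described. Section 7.8 also asks for labelling according to trial procedures, which neither states nor excludes masking to arm. Exposure is low, and a sentence confirming coded labels is all that is needed.

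**The case against.** The strongest reply is that the open-label design is declared and defended as a pilot choice. The primary endpoints are feasibility and acceptability. Fibroscan and CT are secondary, CT has a single follow-up time, and section 10.1 says p-values will not be presented. ELF, the only marker in the sample-size text, is the least exposed, and the use section 10.1 names for a later trial is estimating variability of the effect on ELF. Section 3.1 leaves efficacy to a later trial: confirmed feasibility "will support the establishment of larger, double-blind, placebo-controlled RCT to assess the efficacy of this intervention definitively". All of this stands and limits the consequence. It does not answer the point, because a planned interval estimate can be biased whether or not a p-value accompanies it.

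It is also fair to object that the protocol nowhere says that Fibroscan or CT readings depend on operator or reader. That is a premise of this point.

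Three stronger readings are tempting, and the protocol does not support them:
- A reader might infer that blinding was dropped because participants could not be blinded. Section 7.4 says only that a placebo is not essential, and sections 3.1 and 7.4 both foresee a blinded, placebo-controlled trial.
- A reader might infer that the ELF assay is run with knowledge of the arm. Silence about masking a remote laboratory does not show exposure, and the Laboratory Manual is not at hand.
- A reader might infer that staff who dispense maraviroc will take the scans. Section 8.4 places stock and accountability with the trials pharmacy, and nothing assigns the Fibroscan to anyone. The overlap is not excluded, but it is not planned either.

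**Conclusion.** The point holds in a limited form. Section 7.4 excludes all blinding on grounds that do not reach outcome assessment, so the protocol provides for no masked assessment of the follow-up Fibroscan or the optional CT. Any shift at follow-up that differs by arm would pass undiluted into the between-arm difference.

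Its size cannot be estimated from the protocol. A figure in kPa or percentage points would rest on an assumed shift and, for CT, an assumed number scanned. The conclusion assumes that operators and readers have some discretion over the recorded value and that some of them will know the arm. It is confined to secondary outcomes of a feasibility pilot. This makes it a cheap improvement to the conduct of the trial. It does not invalidate the design, and the open-label choice can stay.

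**What to change.** Replace the opening sentence of section 7.4 with wording such as:

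> Participants and treating staff are not blinded. CT readers receive the scan without allocation. Fibroscan requests carry no allocation and, where existing staffing allows, the operator is not involved in dispensing or counting maraviroc; operator awareness of allocation is recorded in the eCRF. ELF samples carry study number and visit code only.

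The two existing reasons can remain as the case for omitting a placebo.

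The cost is an edit to section 7.4, matching lines in the Laboratory Manual and imaging request forms, and one eCRF field. No visit or assessment is added. No staff are added either, since the separation of roles applies only where present staffing permits.

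The limit is that at small sites the Fibroscan operator may still know the arm. The eCRF field does not prevent that, but it lets the report show how often it happened.

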## 7.5 Baseline data

The following baseline visit data will be collected:

- ☐ Targeted physical examination including BMI, weight, waist circumference
- ☐ Concomitant medicines check
- ☐ Blood draw for FBC, U+Es, LFTs, phosphate, CK,
- ☐ Blood draw for ELF score
- ☐ Blood draw for HIV-1 CCR5 coreceptor tropism (if no result in the previous 24 weeks)
- ☐ Urinary pregnancy test (WOCBP only) and dipstick
- ☐ eCRF completion including data transfer
- ☐ CLDQ:NAFLD, SF36, WPAI:SHP questionnaires
- ☐ Dietary history (daily intake of olive oil, fruit, vegetables or salad, legumes, fish, wine, meat, white bread, rice and whole-grain bread)[23] and exercise history (**number of times per week exercise is undertaken, number of minutes of exercise per episode and type of exercise**)
- ☐ Fasted glucose
- ☐ Fasted lipids (total cholesterol, LDL, HDL, triglycerides)
- ☐ CT liver : spleen attenuation ratio (*optional*) following the protocol for an unenhanced CT abdomen. This may take place within 7 days of the baseline visit, with preference for the 7 days prior.

At baseline, all individuals will also be offered appropriate standard of care interventions regarding their NAFLD diagnosis in line with current NICE guidelines [4]. This will consist of advice regarding dietary modification including offer of referral to dietician; advice regarding exercise recommendations; advice regarding alcohol consumption with respect to national recommended limits and offer of referral to alcohol services where indicated. In addition, referral to the HIV/hepatology joint clinic or other specialist service will be recommended where appropriate.

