| CT liver:spleen attenuation ratio |   | X |   |   |   |   | X |   |
| Drug dispensation                 |   | X | X | X | X | X |   |   |

- 1 Wk 4 visit only for individuals receiving maraviroc. Bloods are unfasted.
- 2 HR, RR, Temp, BP, Lying and standing BP (postural BP at screening only and to be repeated if history indicates)
- 3 Height only at screening; weight and waist circumference at every visit except week 4
- 4 Symptom directed physical examination only
- 5 Point of care urine dip for haematuria, proteinuria, glycosuria, leucocytes and nitrites
- 6 If no result within the preceding 24 weeks
- 7 Haemoglobin, white cell count and differential, eosinophils, platelets
- 8 Sodium, potassium, chloride, creatinine, urea, alanine aminotransferase (ALT), aspartate aminotransferase (AST), bilirubin, alkaline phosphatase (ALP), gamma glutamyltransferase (GGT), albumin, phosphate, CK, glucose (screening, weeks 4, 24 and 72); lipids (total cholesterol, HDL, LDL, triglycerides) (weeks 24 and 72 only)
- 9 Fasting glucose and fasting lipids (total cholesterol, HDL, LDL, triglycerides)
- 10 HbA1c
- 11 anti-HCV Ab, HCV RNA or HCV antigen, HBsAg; if no prior record of result: anti-HBcAb. HIV Ab/Ag only if no previous documented result
- 12 If no previous record of result: INR, ferritin, caeruloplasmin, copper, thyroid function, alpha-1 antitrypsin, anti-mitochondrial antibodies, anti-nuclear antibodies, anti-smooth muscle antibody, anti-liver/kidney/microsomal antibodies-1, coeliac serology
- 13 If no previous imaging (US, CT, MRI) or liver biopsy result confirming fatty liver in the preceding 24 weeks. This may be performed at any point between the screening and baseline visits.
- 14 Includes both median stiffness and controlled attenuation parameter scores. This may be performed at any point between the screening and baseline visits. For the week 48 and 96 week visits, to be performed within 7 days of the study visit.
- 15 Optional. To be performed within 7 days of the study visit. Preference is for the 7 days prior to baseline.
- 16 Only for individuals assigned to the maraviroc group

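### The optional baseline CT may be taken up to 7 days after open-label randomisation, so whether a participant has a baseline scan can depend on the allocated arm

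*Protocol*

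**What the plan says.** Three places in the protocol set the timing of the baseline CT, and they agree:

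- Section 7.5: "This may take place within 7 days of the baseline visit, with preference for the 7 days prior".
- Section 7.6: "This may be performed within 7 days of the study visit with preference for the 7 days prior to baseline".
- Table 1, footnote 15: "Optional. To be performed within 7 days of the study visit. Preference is for the 7 days prior to baseline".

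Each allows the scan on either side of the baseline visit. The days before are preferred but not required.

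Several other things happen at that visit. Section 7.3 states that "subjects will be randomised 1:1 into the maraviroc and non-maraviroc groups (Groups A and B respectively) at the baseline visit (day 1"). Section 7.3.1 adds that "Investigators are immediately shown the treatment allocation", and section 7.4 that "Blinding will not be used". Table 1 marks the first drug dispensing, for the maraviroc group, in the baseline column.

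The scan feeds secondary endpoint (d) in section 3.3, the change by 96 weeks in the percentage with a ratio below 1.0, compared between groups. It is also one of the baseline comparability variables in section 10.3.1. Sections 10.3.2 and 10.4 restrict analysis to available data.

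**The concern.** Randomisation protects a comparison when the people compared are determined before anyone knows the arm. Here the test is voluntary, the arm is known to participant and investigator, and the window stays open for 7 days afterwards. Someone who has just learned that they will continue OBT alone may be less inclined to attend for a scan that Appendix 1 describes as a small additional radiation risk. The documents do not show that this happens, but nothing in them prevents it.

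The open-label rationale in section 7.4 does not cover the point. It argues that the arms are unlikely to differ in behaviour that affects fibrosis, such as diet, exercise and alcohol. It says nothing about willingness to have an optional test.

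A participant without a baseline CT has no change value for endpoint (d). If opting in differs by arm, and is related to liver fat, the two CT groups already differ at baseline for reasons other than chance.

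**Working it through.** **Order of events.** The protocol states no figure on this point, so the check is one of sequence.

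| Step | When | Source |
|---|---|---|
| Consent and screening | up to 42 days before baseline | Table 1; 7.1.2 |
| Screening ultrasound (if needed) and Fibroscan | between screening and baseline visits | Table 1, footnotes 13 and 14 |
| Randomisation, arm shown at once | baseline visit, day 1 | 7.3; 7.3.1 |
| First dispensing (maraviroc group) | baseline visit | Table 1 |
| Optional baseline CT | 7 days before to 7 days after baseline | 7.5; 7.6; Table 1, footnote 15 |
| Optional second CT | week 96, within 7 days | 7.6; Table 1, footnote 15 |

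Of the imaging tests, only the CT has a baseline window that runs past allocation, and it is the one that every participant is free to decline. No section requires it before randomisation or before the first dose.

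**Illustration of size.** None of the following inputs except the 30 per group (section 10.1) is in the documents.

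- p: true share with ratio below 1.0, taken as 0.3 to 0.7.
- Uptake of the scan: 0.9, except as stated next.
- q: share of scans left until after allocation.
- u: uptake after allocation among OBT participants with ratio 1.0 or above.

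The maraviroc group then shows p. The OBT group shows

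p × 0.9 / [p × 0.9 + (1 − p) × ((1 − q) × 0.9 + q × u)].

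Worked case with p = q = u = 0.5. The numerator is 0.5 × 0.9 = 0.45. The second term is 0.5 × (0.45 + 0.25) = 0.35. The OBT share is 0.45 / 0.80 = 0.5625, a spurious baseline difference of about 6 percentage points. The OBT number scanned is 30 × 0.80 = 24, against 30 × 0.9 = 27 in the maraviroc group.

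| q | u | Spurious baseline difference, p from 0.3 to 0.7 |
|---|---|---|
| any | 0.9 | 0 |
| 0.25 | 0.7 to 0.5 | about 1 to 3 points |
| 0.5 | 0.7 to 0.5 | about 2 to 6 points |
| 1.0 | 0.7 to 0.5 | about 5 to 14 points |

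Across the rows with u below 0.9, the OBT group scanned is 18.6 to 26.6 of 30.

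The model makes late uptake depend on the ratio as well as on the arm. If knowing the arm lowered OBT uptake equally at every ratio, numerator and denominator would shrink by the same factor. The share would stay at p and only the number scanned would fall.

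**Exposure before a late scan.** At most 7 days out of 96 × 7 = 672, or 1.0% of the treatment period.

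**The case against.** The protocol prefers the earlier timing in all three places, so most scans may well precede randomisation. The last row of the illustration, with every scan late, runs against that preference and should not be taken as likely. Consent is taken at screening, and agreement to the CT may be recorded then; the consent pages are not shown. This weakens the concern but does not remove it, because agreement in advance does not fix whether or when the scan is done. The endpoint is one optional secondary measure in a pilot whose primary outcomes are feasibility and which presents no p-values. All of this limits the importance of the point.

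Two stronger readings are tempting.

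- A reader might infer that the baseline value itself is distorted by treatment. The documents give no figure for how far the ratio could move in 7 days, the exposure is 1.0% of the treatment period, and the outcome is dichotomised at 1.0. A material effect is unlikely.
- A reader might infer that moving the scan before randomisation would settle the whole CT comparison. It would not. Section 7.6 makes the week 96 scan optional too, and the early termination visit has no CT in either Table 1 or section 7.6. Who contributes both scans still depends on choice and retention long after the arm is known, and that may be the larger route for selection.

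There is also a case against scanning at any time in the 42-day screening period. Section 10.2 expects 1 to 2 screen failures a month out of 4 to 5 people, so an open window could expose people who never enter the trial to radiation. That objection stands, and it shapes the fix.

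**Conclusion.** The point holds in a limited form. The protocol permits an optional baseline scan after open allocation and first dispensing, so who has one can depend on the arm. This follows directly from sections 7.3 to 7.6 and Table 1.

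The size is not estimable from the documents. The illustration gives 0 if uptake does not depend on arm and about 1 to 6 percentage points if a quarter to a half of scans are late. It rests on assumed uptake, timing and direction, and on late uptake being related to the ratio. The documents do not show that arm-dependent uptake will occur. The consequence is confined to endpoint (d) and the baseline CT summary, and the feasibility outcomes are unaffected. This is a minor point, worth making because it can be corrected by wording.

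**What to change.** In Table 1 footnote 15 and sections 7.5 and 7.6:

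- Require the optional baseline CT, or a recorded decision to decline it, to be complete before the randomisation form described in section 7.3.1 is submitted.
- Keep the existing 7 days before baseline, and scan only once the eligibility results are in.
- Do not treat a scan dated after randomisation as a baseline value. Report the number of such scans by arm.
- Report by arm how many participants have a baseline scan, a week 96 scan and both, because selection at week 96 remains.

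The cost is a change of wording, with no added visit, scan or participant. A few optional scans may be lost if they cannot be booked before randomisation, and an occasional person who is scanned may not go on to be randomised. Excluding late scans at analysis alone would be weaker: it removes values taken after allocation but does not recover participants who put off the scan and then did not have it.
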